## Abstract

**Background:**

The *al-Andalus *physical activity intervention study is a randomised control trial to investigate the effectiveness of a land- and water-based exercise intervention for reducing the overall impact of fibromyalgia (primary outcome), and for improving tenderness and pain-related measures, body composition, functional capacity, physical activity and sedentary behaviour, fatigue, sleep quality, health-related quality of life, and cognitive function (secondary outcomes) in women with fibromyalgia.

**Methods/Design:**

One hundred eighty women with fibromyalgia (age range: 35-65 years) will be recruited from local associations of fibromyalgia patients in *Andalucía *(Southern Spain). Patients will be randomly assigned to a usual care (control) group (n = 60), a water-based exercise intervention group (n = 60) or a land-based exercise intervention group (n = 60). Participants in the usual care group will receive general physical activity guidelines and participants allocated in the intervention groups will attend three non-consecutive training sessions (60 min each) per week during 24 weeks. Both exercise interventions will consist of aerobic, muscular strength and flexibility exercises. We will also study the effect of a detraining period (i.e., 12 weeks with no exercise intervention) on the studied variables.

**Discussion:**

Our study attempts to reduce the impact of fibromyalgia and improve patients' health status by implementing two types of exercise interventions. Results from this study will help to assess the efficacy of exercise interventions for the treatment of fibromyalgia. If the interventions would be effective, this study will provide low-cost and feasible alternatives for health professionals in the management of fibromyalgia. Results from the *al-Andalus *physical activity intervention will help to better understand the potential of regular physical activity for improving the well-being of women with fibromyalgia.

**Trial registration:**

ClinicalTrials.gov ID: NCT01490281

## Background

Fibromyalgia is becoming a common syndrome in Western European countries since a point prevalence of 2.9% would translate to approximately 6 million people with fibromyalgia [1]. The prevalence of fibromyalgia in Spain is ~2.4%, and is more common in women (~4.2%) than in men (~0.2%) [2].

Fibromyalgia is considered a disorder of pain regulation [3], as indicated by an increased sensitivity to painful stimuli (hyperalgesia) and lowered pain threshold (allodynia) [4]. Additionally to pain, fibromyalgia symptoms typically include fatigue, stiffness, non-restorative sleep patterns, and memory and cognitive difficulties [5-7]. Other common symptoms are low back pain, recurrent headaches, muscle-spasm, and balance problems [5]. The prevalence of comorbidities among patients diagnosed with fibromyalgia is very high [8], which increases patients' needs for appropriate medical management and results in higher healthcare resource utilization compared with persons without fibromyalgia [9].

Fibromyalgia has an important impact on the patients' health-related quality of life [10,11], since it limits activities of daily life such as walking or raising and transporting objects [11,12]. In general, functional capacity is decreased in adults with fibromyalgia [13-18] and is similar to that of healthy elderly [16,19]. Jones et al. [19] reported that women with fibromyalgia have difficulties for staying physically independent.

Exercise therapy is relatively economical, easily accessible and widely used in clinical practice as a strategy for pain management. Several reviews concerning the effect of exercise in fibromyalgia patients concluded that: i) there is moderate evidence that aerobic exercise produces important benefits in physical function, pain and tender points [20,21]; ii) there is limited evidence that strength training improves pain, global wellbeing, physical function, tender points and depression [22]; and iii) there is not enough evidence regarding the health-related effects of flexibility exercises [22]. A recent meta-analysis [23] concluded that exercise (aerobic, strength training or both) improves global well-being, assessed by the fibromyalgia impact questionnaire (FIQ) in women with fibromyalgia. The Ottawa Panel supports the use of aerobic exercise interventions and strengthening exercises for the overall management of fibromyalgia [24,25].

Exercise therapy in fibromyalgia patients has usually focused on either pool or land-based exercises. A recent meta-analysis [26] indicated that there is no evidence that water-based aerobic exercise produces superior results compared to similarly intense land-based exercise. Others narrative reviews however suggested slight additional benefits for water-based aerobic exercise on reducing pain and improving depressive symptoms [27], sleep quality and mood [20]. Jentoff et al. [28] compared the effect of a 20-week pool-based exercise and a land-based exercise intervention (twice a week) on symptoms, self-efficacy, self-reported physical impairment, and physical capacity in a group of fibromyalgia patients. They observed significant improvements in cardiovascular capacity and walking time in both exercise groups. The pool-exercise group also improved self-reported physical impairment, number of days feeling good, pain, anxiety, and depression. To our knowledge, the study by Jentoff et al. [28] is the only available study investigating the possible additional beneficial effects of exercising in a warm-water pool (compared to land-based) in fibromyalgia patients. More studies comparing the effectives of a water-based exercise program with a land-based exercise intervention on a broader range of physical and psychological outcomes and with longer intervention period, higher frequency, and larger samples are needed.

It is of public health and clinical relevance to better understand whether the benefits of land-based exercise are similar to those observed with exercise undertaken in water, owing to the low availability of pools with an appropriate water temperature for these patients, ideally between 30 and 33°C.

### Objectives

The primary objective of the *al-Andalus *physical activity randomised controlled trial (RCT) is to investigate the effectiveness of two types of exercise interventions (water- and land-based aerobic-strength training vs. a control group) on the overall impact of fibromyalgia (primary outcome), and on tenderness and pain-related measures, body composition, functional capacity, physical activity and sedentary behaviour, fatigue, sleep quality, health-related quality of life and cognitive function (secondary outcomes) in women aged 35-65 years with fibromyalgia. The intervention groups will train 3 days/week (60 min per session) for a 24-week period. We will also study the effect of a detraining period (i.e., 12 weeks with no exercise intervention) on the studied variables.

## Presentation of the hypothesis

We hypothesised that: (i) a 24-weeks exercise intervention training (either water- or land-based) would be effective for reducing the impact of fibromyalgia (primary outcome), and improving tenderness and pain-related measures, body composition, functional capacity, physical activity and sedentary behaviour, fatigue, sleep quality, health-related quality of life and cognitive function (secondary outcomes) in women with fibromyalgia; (ii) a 24-weeks land-based aerobic-strength intervention training could be as effective as a water-based intervention; and (iii) the exercise training-induced gains would be partially retained in the intervention groups after the detraining period such that their physical status will still be better than that of the control group at this time point.

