### Sample size

The required sample size was determined for the primary outcome variable, i.e. overall score of Fibromyalgia Impact Questionnaire (FIQ) [30]. According to previous research [31], a clinically relevant change is a 15-20% reduction in the total FIQ score (which equals to a ~10-15 points reduction). Assuming an unilateral alternative (i.e. the intervention reduces impact of fibromyalgia), we can detect differences of at least 15% with a power of 95% and α of 0.05 with two groups (intervention and usual care group) of 45 participants, with a mean in the FIQ of ~70 and a standard deviation of ~20 points. Assuming a maximum lost of follow-up of 30%, we will recruit a total of 60 women with fibromyalgia for each group. Since we will develop two types of interventions (land and water-based), we will recruit a total of 180 women with fibromyalgia (i.e., two intervention groups and one usual care group of 60 persons each). Figure 1 shows the flow diagram of the study participants

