### Statistical analysis

For between groups comparisons at baseline (usual care vs water-based intervention vs land-based intervention), we will analyse continuous variables with one-way analysis of variance or the non-parametric method of Kruskall-Wallis, and Chi-square tests (or exact techniques if needed). We will use analysis of covariance (ANCOVA) to assess the training effects on the primary and secondary study outcomes (or the rank-transform ANCOVA). Age and baseline level of each outcome variable will be entered as covariates. For each outcome variable we will report the effect size and the level of significance corresponding to the main group (between-subjects), time (within-subjects) and interaction (group × time) effects.

We will adjust multiple comparisons for mass significance [32]. We will also examine the differences between drop-outs and participants who remain in the study. We will analyse the data according to the intention-to-treat principle [33]. We will handle missing data due to drop-outs or non-compliance using multiple imputation methods. To fully appreciate the potential influence of missing responses, we will perform sensitivity analysis. In all analyses, we will study the effect of the regression towards the mean.

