## Implications of the hypothesis

The *al-Andalus *physical activity RCT will investigate the effects of 24-week land- and water-based exercise interventions on disease impact, tenderness, body composition, functional capacity, quality of life and cognitive function in female patients with fibromyalgia. Both exercise interventions will include aerobic, strengthening and flexibility exercises. We will also assess the effect of a 3-month detraining period on the study primary and secondary outcomes. To our knowledge, this is the largest study specifically designed to compare the effect of a water-based and land-based exercise interventions on fibromyalgia patients. Our study attempts to reduce impact of fibromyalgia and improve patients' health status and quality of life by implementing two types of exercise interventions. Results from this study will help to better assess the potential of exercise interventions in the treatment of fibromyalgia. If the interventions proved to be effective and safe, this study would provide low-cost and feasible alternatives for health professionals in the management of fibromyalgia.

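### Hypothesis (ii), that land training could match water training, has no stated criterion: the only analysis given tests for a difference and the sample is sized only against usual care

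*Protocol article*

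**What the plan says.** Three parts of the protocol article bear on the land-water comparison.

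- **Purpose.** Under Presentation of the hypothesis, the second of three numbered hypotheses is that "a 24-weeks land-based aerobic-strength intervention training could be as effective as a water-based intervention". The Background gives the motive: pools at a suitable temperature are scarce, so it matters to "better understand whether the benefits of land-based exercise are similar to those observed with exercise undertaken in water". Implications of the hypothesis adds that, to the investigators' knowledge, "this is the largest study specifically designed to compare the effect of a water-based and land-based exercise interventions on fibromyalgia patients". The Objectives section frames the primary objective differently, as "water- and land-based aerobic-strength training vs. a control group".
- **Sample size.** The calculation is made "with two groups (intervention and usual care group) of 45 participants". It is one-sided: "Assuming an unilateral alternative (i.e. the intervention reduces impact of fibromyalgia". A second exercise arm of the same size is then added. The section contains no land-water calculation. Its only clinical threshold is that "a clinically relevant change is a 15-20% reduction in the total FIQ score (which equals to a ~10-15 points reduction".
- **Analysis.** The Statistical analysis section says: "We will use analysis of covariance (ANCOVA) to assess the training effects on the primary and secondary study outcomes", with age and the baseline value as covariates. Effect size and significance level are to be reported for group, time and their interaction. Multiple comparisons will be adjusted. The section names no margin and no confidence-interval rule for any contrast.

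**The concern.** Hypothesis (ii) is a statement of similarity. The group, time and interaction tests all take no difference as the null hypothesis. Rejecting that null speaks against hypothesis (ii); failing to reject it leaves the matter open. So the stated method cannot support the stated hypothesis, whatever the data show. The sample size does not close the gap, because it was set for a superiority question against a different comparator.

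This has practical weight because the land-water question is the one that decides whether land training can stand in for scarce pools. If no criterion is fixed in advance, the easiest route to a favourable conclusion is a non-significant land-water contrast, and a smaller or noisier trial produces one more readily. The multiplicity adjustment pushes the same way: a stricter significance threshold makes non-significance more likely.

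**Working it through.** **Inputs from the Sample size section:** mean FIQ about 70; SD about 20; smallest relevant change 15% of 70 = 10.5 points; 45 completers per arm; 60 recruited per arm with up to 30% loss, so 60 × 0.7 = 42 completers at the worst planned loss. Higher FIQ is worse, so a positive land minus water difference means that land does worse.

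**Assumption of this review:** the plan adjusts for baseline but gives no correlation. An adjusted SD of 16 is shown alongside 20; it corresponds to a baseline correlation of 0.6, since 20 × √(1 − 0.6²) = 16.

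**1. The plan's own figure.** n per group = 2 × (1.645 + 1.645)² × 20² / d², for one-sided 5% and 95% power.
- d = 10.5 (15%): 78.5, so 79 per group. With 45 per group the power is about 80%.
- d = 14 (20%): 44.2, so 45 per group.

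The stated 45 therefore matches a 20% difference, not the stated 15%, unless an unstated baseline correlation of about 0.66 was used. That is a separate matter. What counts here is that both versions concern exercise against usual care.

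**2. Precision of land minus water.** SE = SD × √(2/n); 95% half-width = t(0.975, 2n − 2) × SE.

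| SD | n per arm | SE | t | Half-width (FIQ points) |
|---|---|---|---|---|
| 20 | 45 | 4.22 | 1.987 | 8.4 |
| 20 | 42 | 4.36 | 1.989 | 8.7 |
| 16 | 45 | 3.37 | 1.987 | 6.7 |
| 16 | 42 | 3.49 | 1.989 | 6.9 |

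**3. Chance of a non-significant land-water result when land is truly worse.** Two-sided 5% test, unadjusted for multiplicity, from the noncentral t distribution with noncentrality d/SE. For example, d = 5, SD 20 and n = 45 give 5/4.22 = 1.19 and a probability of 0.78.

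| True deficit of land | SD 20, n = 45 / 42 | SD 16, n = 45 / 42 |
|---|---|---|
| 5 points | 78% / 80% | 69% / 71% |
| 10.5 points | 31% / 34% | 13% / 16% |

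**4. What a margin-based claim could achieve.** The protocol gives no margin, so those below are illustrative. The table shows the power for the upper 95% confidence limit of land minus water to fall below the margin, with no true difference and SD 20.

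| Margin | n = 45 | n = 42 |
|---|---|---|
| 5 points | 22% | 20% |
| 7 points | 38% | 35% |
| 10.5 points | 69% | 66% |

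At 10.5 points and SD 16 the power would be 87% / 84%. But 10.5 points is the whole clinically relevant change, so a margin of that size would let land lose almost all of a relevant benefit and still pass.

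**The case against.** The strongest case against the point has five parts.

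- **No misreading is planned.** A reader might infer that the investigators intend to treat a non-significant land-water result as proof of equal effectiveness. The article does not say so. It gives no decision rule for hypothesis (ii) at all, so the inference is not supported. What stands is that the criterion is absent.
- **Not purely p-value driven.** The plan commits to reporting effect sizes as well as significance levels. That is correct and helpful, but an effect size without a margin or interval rule does not establish similarity.
- **Not the primary contrast.** The primary objective compares exercise with control, and hypothesis (ii) is worded cautiously. Sizing on the primary contrast is normal practice. This lowers the severity. It does not remove the mismatch, because the article also presents the study as designed for the land-water comparison.
- **Detail for a fuller document.** A margin could sit in a full protocol or SAP that is not shown. Its mere absence would be no finding. But hypothesis, sizing and analysis method are all fixed in this article, and they do not fit together.
- **Unfavourable inputs.** SD 20 ignores the planned baseline adjustment. With SD 16 the figure at a 10.5-point deficit falls to 13-16%, which weakens the concern for large deficits. At 5 points it remains 69-71%.

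It is also tempting to call this a non-inferiority question outright. The Background asks whether benefits are similar, which fits estimation or two-sided equivalence equally well.

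**Conclusion.** The point holds in a limited form. The stated analysis can contradict hypothesis (ii) but cannot support it, no alternative criterion is given, and the trial was not sized for this contrast. That the investigators would misread non-significance is not established.

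Non-significance would carry little information. At SD 20 and 42 to 45 completers per arm it occurs in roughly four of five trials at a true 5-point deficit and in about one of three at 10.5 points. These figures rest on the protocol's SD, a two-sided 5% test without multiplicity adjustment, and completers only. The SD of 16 is assumed. The weakness should be corrected, but it does not touch the primary comparison with usual care.

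**What to change.** In the Statistical analysis section, state that hypothesis (ii) will be addressed by the baseline-adjusted land minus water difference in FIQ at week 24 with its 95% confidence interval, and that a non-significant difference will not be taken to show equal effectiveness.

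Allow a claim of equal effectiveness only if two conditions are met. First, before results are known, the investigators justify a margin clearly smaller than the 10.5-point clinically relevant change. Second, the confidence limit unfavourable to land (the upper limit of land minus water) lies inside that margin. State the achievable power next to the margin. If no margin can be justified, reword hypothesis (ii) as estimation.

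The cost is a few sentences and no extra patients. The downside is that power is low at margins of 5 to 7 points (20-38% at SD 20), so the trial will probably be able to report only an estimate of the land-water difference and not a claim of equal effectiveness.

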## Testing the hypothesis

The present study is a RCT (ClinicalTrials.gov ID: NCT01490281). The Medical Ethics Committee of *Hospital Virgen de las Nieves *(Granada, Spain) approved the study design, study protocols and informed consent procedure. All participants have to provide a written informed consent. After baseline measurements, they will be randomly allocated to the usual care (control), land-based training or water-based group. The participants will be followed for 24 weeks during the training interventions and after 12 weeks of training cessation. All the baseline and follow-up examinations will be performed in the same setting (local association of fibromyalgia patients) and by the same investigators. The study will be performed following the ethical guidelines of the Declaration of Helsinki, last modified in 2000.

### Participants and selection criteria

Women with fibromyalgia will be recruited from the local associations of fibromyalgia patients in *Andalucía *(Southern Spain). Before starting the study, a screening will be performed of all candidates. The inclusion and exclusion criteria for the study are shown in Table 1.

**Table 1 T1:** Inclusion and exclusion criteria in the *al-Andalus *physical activity trial

*Inclusion criteria*	*Exclusion criteria*
- Age: 35-65 years.	- Acute or terminal illness.

- To be diagnosed with fibromyalgia by a rheumatologist and meeting the American College of Rheumatology criteria: widespread pain for more than 3 months, and pain with 4 kg/cm of pressure reported for 11 or more of 18 tender points [6].	- Myocardial infarction in the past 3 months.

- Not to have other severe somatic or psychiatric disorders, or other diseases that prevent physical loading (Answer "no" to all questions on the Physical Activity Readiness Questionnaire-PAR-Q [29]).	- Unstable cardiovascular disease or other medical condition.

- Not to be engaged in regular physical activity > 20 min on > 3 days/week in the past 3 months.	- Upper or lower extremity fracture in the past 3 months.

- Planning to stay in the same Association during the study.	- Unwillingness to either complete the study requirements or to be randomised into control or training group.

- Able to ambulate without assistance.	- Severe dementia (MMSE < 10)

- Able to communicate.	- Presence of neuromuscular disease or drugs affecting neuromuscular function.

- Informed consent: Must be capable and willing to provide consent.	- To be engaged in other physical or psychological treatment.

### Sample size

The required sample size was determined for the primary outcome variable, i.e. overall score of Fibromyalgia Impact Questionnaire (FIQ) [30]. According to previous research [31], a clinically relevant change is a 15-20% reduction in the total FIQ score (which equals to a ~10-15 points reduction). Assuming an unilateral alternative (i.e. the intervention reduces impact of fibromyalgia), we can detect differences of at least 15% with a power of 95% and α of 0.05 with two groups (intervention and usual care group) of 45 participants, with a mean in the FIQ of ~70 and a standard deviation of ~20 points. Assuming a maximum lost of follow-up of 30%, we will recruit a total of 60 women with fibromyalgia for each group. Since we will develop two types of interventions (land and water-based), we will recruit a total of 180 women with fibromyalgia (i.e., two intervention groups and one usual care group of 60 persons each). Figure 1 shows the flow diagram of the study participants

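### The stated 95% power belongs to one unadjusted, one-sided comparison, not to the three-group, multiplicity-adjusted analysis that the protocol plans

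*Protocol article*

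**What the plan says.** Protocol article, Sample size. The calculation is for the FIQ total score and rests on a directional alternative: "Assuming an unilateral alternative (i.e. the intervention reduces impact of fibromyalgia"). Its claim is that "we can detect differences of at least 15% with a power of 95% and α of 0.05". The comparison behind this claim is between "two groups (intervention and usual care group) of 45 participants". The distribution of scores that it assumes is given as "with a mean in the FIQ of ~70 and a standard deviation of ~20 points". Relevance is defined just before: "a clinically relevant change is a 15-20% reduction in the total FIQ score (which equals to a ~10-15 points reduction"). The size is then raised for loss to follow-up ("Assuming a maximum lost of follow-up of 30%, we will recruit a total of 60 women with fibromyalgia for each group") and carried over to a third arm, giving "two intervention groups and one usual care group of 60 persons each". Alpha is not changed when the second exercise arm is added.

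Protocol article, Statistical analysis. Training effects are to be assessed by ANCOVA with age and the baseline value of the outcome as covariates. Effect sizes and significance levels are to be reported for group, time and group-by-time effects. The section adds: "We will adjust multiple comparisons for mass significance". It mentions no one-sided test, and it does not say which comparisons are adjusted or by what method.

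Protocol article, Presentation of the hypothesis. Hypothesis (i) is that either form of exercise is effective. Hypothesis (ii) is that land-based training could be as effective as water-based training.

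**The concern.** A power figure is tied to a test: its contrast, its sidedness and its alpha. The Sample size section fixes all three for a two-group comparison. The Statistical analysis section describes something else: three groups, group effects that are normally tested without direction, and an adjustment for multiple comparisons. Both positions are stated in the same article, so this is a conflict between two commitments and not a detail left to a fuller document.

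If the analysis follows the Statistical analysis section, a non-significant result in one exercise arm could be read as coming from a trial with 95% power when the power of that comparison was lower. If the one-sided 5% test is kept instead so that the figure still applies, each contrast has a 5% chance of a false claim in favour of exercise, against 2.5% with a two-sided 5% test, and there are two such contrasts.

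**Working it through.** **Inputs from the Sample size section.** Mean FIQ about 70, SD about 20, 45 per group, alpha 0.05, one-sided. In points, 15% of 70 = 10.5 and 20% of 70 = 14.

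**Method.** For a two-group comparison the noncentrality is δ = d / (SD × √(2/n)). Power is the probability that a noncentral t variable with 2n − 2 = 88 degrees of freedom exceeds the critical value (the opposite tail of the two-sided tests is negligible here).

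**Step 1: reproduce the stated figure.** With n = 45, SD × √(2/n) = 20 × √(2/45) = 4.216. The one-sided 5% critical value is 1.662.
- 14 points: δ = 14 / 4.216 = 3.32, power 95%. The stated figure reproduces here.
- 10.5 points: δ = 10.5 / 4.216 = 2.49, power 80%. The stated figure does not reproduce at the 15% difference that the text names. That is a separate error.

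The cost of the mismatch alone is therefore measured at 14 points, where the article's own calculation works.

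**Step 2: change the test; keep 14 points, SD 20 and n = 45.**

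| Test | Critical value | Power |
|---|---|---|
| One-sided 0.05, one contrast (as sized) | t = 1.662 | 95% |
| Overall three-group F-test at 0.05, both exercise arms equally effective | F = 3.065 | 93% |
| Two-sided 0.05, one contrast | t = 1.987 | 91% |
| Two-sided, Bonferroni for two (0.025 each) | t = 2.280 | 85% |
| Two-sided, Bonferroni for three (0.0167 each) | t = 2.441 | 81% |

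For the F-test the group means are 0, 14 and 14 below control. The noncentrality is n × (2/3) × d² / SD² = 45 × (2/3) × 196 / 400 = 14.7, on 2 and 132 degrees of freedom. Dunnett's two-sided test for two contrasts gives 87% (normal approximation, critical value 2.212); Bonferroni for two gives 86% on the same approximation.

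**Step 3: allow for baseline adjustment.** ANCOVA on baseline reduces the SD to 20 × √(1 − ρ²), where ρ is the correlation between baseline and follow-up. The article gives no ρ, so 0.5 and 0.6 are assumed here. They give SDs of 17.32 and 16.0. Two-sided Bonferroni for two, n = 45:

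| Difference | ρ = 0 | ρ = 0.5 | ρ = 0.6 |
|---|---|---|---|
| 14 points | 85% | 94% | 97% |
| 10.5 points | 58% | 72% | 80% |

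**The case against.** The strongest reply has four parts.

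1. *The planned test is not fully specified.* The Statistical analysis section does not use the word F-test, does not say two-sided, and does not name the adjusted family or method. A directional contrast within the ANCOVA is not excluded, and the adjustment might concern the many secondary outcomes. This stands. F-tests are a fair inference from group and interaction effects over three groups, but the Bonferroni figures are scenarios. The loss must be given as a range, and its lower end, the overall F-test, is only about 2 percentage points. That test does not, however, show which exercise arm works.

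2. *Baseline adjustment is planned and recovers power.* This stands in part. At 14 points and a correlation of 0.5–0.6 it roughly offsets the multiplicity loss. But the calculation does not invoke it and the article gives no correlation. At 10.5 points, power stays below 95% with both assumed correlations.

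3. *Low figures such as 58% mix in another fault.* This also stands. At 10.5 points the one-sided, unadjusted test already has only 80%. Likewise, 60 recruited less 30% leaves 42 and not 45, which is a separate matter. Neither is charged to this point.

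4. *One-sided sizing was openly declared and matches hypothesis (i).* True. A reader might infer that the one-sided calculation is wrong because it does not fit the land-versus-water hypothesis, or that the trial will run a one-sided 5% test and so double the usual false-positive rate. The article supports neither reading. The calculation sized exercise against control, not hypothesis (ii), and the Statistical analysis section does not commit to a one-sided final test.

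**Conclusion.** The point holds. The Sample size section makes no allowance for the second exercise-versus-control contrast or for the adjustment that the Statistical analysis section promises, so its 95% is not the power of the planned primary analysis.

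The mismatch alone, at 14 points with SD 20, 45 per group and no covariate gain, takes power from 95% to between 93% and 81%, depending on the test. With two adjusted two-sided contrasts, the chance of missing a true 14-point effect in a given arm rises from 5% to 15%. If the unstated baseline correlation were 0.5–0.6, power for those contrasts would be 94–97%.

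It would go too far to say that the primary analysis is known to have 50–60% power. That range requires the 10.5-point difference, an adjustment scheme that the article does not name, and no gain from baseline adjustment. What can be said is that the stated power and the stated analysis do not belong together, and that the text as written does not let a reader work out the actual power.

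**What to change.** - Name the two exercise-versus-usual-care contrasts of week-24 FIQ as the primary comparisons.
- Use the same sidedness and the same multiplicity-adjusted alpha in the Sample size and Statistical analysis sections. Two-sided testing with Dunnett or Holm at a family-wise 0.05 is one suitable choice; the documents do not require that particular method.
- Restate the power for that test at the planned number per group, for a difference given in points. If the gain from baseline adjustment is counted, state the assumed correlation.
- Say whether the land-versus-water comparison lies inside or outside the adjusted family.

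The cost is revised wording and a less favourable stated power. No extra patients are needed.

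### On its own inputs, 45 women per group gives about 80% power for a 15% FIQ difference, not the stated 95%, and 30% loss from 60 leaves 42, not 45

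*Protocol article*

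**What the plan says.** The Sample size section of the protocol article bases the trial's size on the total FIQ score, the primary outcome, with a one-sided alternative. It describes clinical relevance as follows: "a clinically relevant change is a 15-20% reduction in the total FIQ score (which equals to a ~10-15 points reduction"). It then states that "we can detect differences of at least 15% with a power of 95% and α of 0.05 with two groups", specified as "with two groups (intervention and usual care group) of 45 participants", and gives the planning values "with a mean in the FIQ of ~70 and a standard deviation of ~20 points".

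On attrition it says: "Assuming a maximum lost of follow-up of 30%, we will recruit a total of 60 women with fibromyalgia for each group". With two exercise arms and one usual care arm, this makes 180 in total.

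The Statistical analysis section plans ANCOVA: "Age and baseline level of each outcome variable will be entered as covariates". Neither section gives a baseline-outcome correlation, a residual SD or an SD of change.

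**The concern.** Every input to the power calculation is printed beside its result, so the sentence can be checked directly, and the two do not agree. The mismatch is in the only power justification for the primary outcome, and it sits at the lower bound of what the authors call clinically relevant. A reader would take it that a true 15% benefit would be missed one time in twenty. On the printed inputs it would be missed about one time in five. That affects how much weight a non-significant FIQ comparison could bear.

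The attrition sentence has a separate, smaller problem: the number recruited does not preserve the number the power statement relies on.

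**Working it through.** **Inputs, all from the Sample size section:** mean FIQ 70; SD 20; difference 15%; one-sided alpha 0.05; power 95%; 45 per group for analysis; 60 per group recruited; loss up to 30%.

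**1. Effect in points.** 0.15 × 70 = 10.5 points, so the standardised difference is 10.5/20 = 0.525.

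**2. Trying to reproduce the stated 95%.** The noncentrality with 45 per group is 0.525 × √(45/2) = 2.49.
- Normal approximation: Φ(2.49 − 1.645) = 80.1%.
- Noncentral t, 88 degrees of freedom: 79.6%.

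The 95% is not reproduced. A two-sided test would give 69.3% (noncentral t).

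**3. Sample size needed for 95% at 15%.** n = 2(1.645 + 1.645)² (20/10.5)² = 78.5, so 79 per group by the normal formula. By noncentral t, 79 gives 94.95%, so 80 are needed.

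**4. Where 45 could come from.** Two calculations return it:
- 20% difference (14 points), 95% power: 2(3.29)² (20/14)² = 44.2, so 45. Noncentral t power at 45 is 95.1%.
- 15% difference (10.5 points), 80% power: 2(1.645 + 0.842)² (20/10.5)² = 44.9, so 45.

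The text does not show which was run.

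**5. Other readings** (noncentral t, one-sided unless noted):

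| Reading | Power |
|---|---|
| Both exercise arms pooled, 90 vs 45, 10.5 points | 88.8% |
| No loss at all, 60 vs 60, 10.5 points | 88.8% |
| 10 points, 45 per group | 76.1% |
| 15 points instead of 15%, 45 per group | 97.0% (two-sided 94.0%) |

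The last row comes close to 95% two-sided, but 15 points is 15/70 = 21% of the mean, and the text specifies 15% and a one-sided alternative. The planning values are marked approximate, but the SD would have to be about 15 rather than 20 for 45 per group to reach 95% at 10.5 points.

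**6. Loss to follow-up.**
- 60 × 0.70 = 42 evaluable.
- 45/0.70 = 64.3, so 65 per group, or 195 in total, to keep 45.
- 1 − 45/60 = 25% is the most that 60 can lose and still leave 45.

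**7. Power at both evaluable sizes** (one-sided 0.05, SD 20, noncentral t):

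| Evaluable per group | 15% (10.5 points) | 20% (14 points) | Difference with 95% power |
|---|---|---|---|
| 45 | 79.6% | 95.1% | 14.0 points (20.0%) |
| 42 | 77.1% | 93.8% | 14.5 points (20.7%) |

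**8. Effect of the planned ANCOVA.** If ρ is the baseline-outcome correlation, the residual SD is 20√(1 − ρ²). The document gives no ρ, so the range is an assumption. For 10.5 points and 45 per group:

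| Assumed ρ | Power |
|---|---|
| 0 | 79.6% |
| 0.3 | 82.8% |
| 0.5 | 88.7% |
| 0.6 | 92.6% |
| 0.66 | 95.0% |

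**The case against.** The strongest reply is that 79.6% describes an unadjusted comparison, whereas the trial will adjust for baseline FIQ and age. At a correlation of 0.5 the power would be 88.7%, and at about 0.66 it would reach the stated figure. This stands as a limit on what can be claimed: a type II error of 20 to 23% follows from the printed inputs, but it is not a firm figure for the planned analysis. It does not rescue the sentence, which quotes a raw mean and SD and no correlation. The same Statistical analysis section also promises adjustment for multiple comparisons, and the sample size makes no allowance for it. That would pull power down by an amount the document does not fix.

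A second reply is that the cause is unknown: the slip may lie in the effect size (20% calculated, 15% written) or in the power (80% calculated, 95% written). That is right, and the authors need to say which. The sentence is wrong in either case.

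A third is that the attrition error is small and that 30% is described as a maximum. Also fair: 42 is the worst case, and going from 45 to 42 costs 2.5 percentage points of power at 15% and 1.3 at 20%. It is a secondary error beside the power statement.

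Finally, nothing in the document says how a null result would be interpreted, so the risk of over-reading one is a reasonable worry and not something the plan proposes.

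**Conclusion.** The concern holds. On the printed inputs (mean 70, SD 20, 15% difference, one-sided 0.05, two groups of 45) power is about 80%, roughly 15 percentage points below the stated 95%. Reaching 95% would need 80 evaluable women per group. The loss allowance is wrong as well: 60 per group with 30% loss leaves 42, three short of the 45 assumed.

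These figures rest on an unadjusted two-sample comparison with no multiplicity correction, because that is all the section specifies. The design itself is adequate for a 20% difference, with 94 to 95% power at 42 to 45 per group. The fault is a materially misreported justification for the primary outcome, and it should be corrected.

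**What to change.** Keep 60 per group and correct the Sample size section:

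- State that 45 evaluable women per group give 95% one-sided power for a 20% (14-point) difference and about 80% for a 15% (10.5-point) difference, and say which calculation was originally run.
- Preferably keep the 30% loss assumption and report 42 evaluable per group, with 94% power for 20% and 77% for 15%. The alternative is to restate the loss allowance as 25%, which is what 60 recruited for 45 evaluable supports.
- If the 15% claim is meant to rely on the ANCOVA, state the assumed baseline-outcome correlation (about 0.66 is needed at 45 per group) and its source.

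This is a text correction. It needs no additional participants and no change to design or analysis. Its only cost is that the stated power becomes less favourable.
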